#### Vital signs and laboratory parameters

For vital signs, the observed data at baseline and change from baseline for each measurement day will be summarized with descriptive statistics.

Summary statistics for actual values and for change from baseline will be tabulated for laboratory results by scheduled visit. Subjects with laboratory values outside of the normal reference range at any post-baseline assessment will be summarized. Shifts from baseline laboratory values (to worst severity per subject) will be tabulated.

#### Physical examinations

Simple descriptive statistics will be used to summarize the physical examination findings by visit.

#### Concurrent medications

A summary of all concomitant medications taken during the course of the study will be presented in tabular form by therapeutic drug class and generic drug name using the World Health Organization (WHO) Drug classification.

### Efficacy analysis

The secondary objectives of the study are to evaluate immune response measured by T cell immunogenicity (ELISPOT and proliferation assays), by DTH and to evaluate CD4 and viral load (HIV-1 RNA).

#### Efficacy endpoints

The efficacy endpoints will be summarized using descriptive statistics. Absolute changes in CD4 counts between study start (mean of screening and week 1 [Baseline] values) and Week 8 will be calculated. Both the values registered at week 8 and the changes from baseline will be compared among the treatment arms using analysis of covariance (ANCOVA) including the baseline value in the model. Additionally, the changes over time will be explored (e.g., investigate if the treatment effect continues to increase over time) using linear models taking into account that repeated measures are taken from each subject. Given the small sample size, the focus of these will be primarily to describe the changes associated with the different Vacc-4x doses together with Endocine relative to changes that would be seen with Endocine only.

A number of secondary endpoints have been defined. These endpoints are a mixture of continuous and binary endpoints. Continuous endpoints will analyze using the same approach as described above. Binary endpoints will be summarized using the Cochran-Mantel-Haenszel test and the normal approximation to the binomial distribution.

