### Secondary objectives

- To evaluate cellular immune responses to Vacc-4x in vitro.
- To evaluate cellular immune responses to Vacc-4x in vivo by DTH in comparison to DTH from unvaccinated patients on effective ART (data from preceding study).
- To evaluate the effect on CD4 counts and viral load (HIV-1 RNA).

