## Inclusion criteria

A subject will be eligible for enrollment in the study if all of the following criteria apply:

- Age above 18 years, both genders.
- HIV positive at least one year.
- Clinically stable on ART for the last 6 months (changes in therapy is allowed as long as the viral load is stable).
- Documented viral load (HIV-1 RNA) less than 50 copies/mL for the last six months.
- Documented stable CD4 cell count ≥ 400x106/L.
- Nadir (lowest ever) CD4 cell count ≥ 200x106/L.
- Signed informed consent.

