## Efficacy assessments

### Delayed type hypersensitivity test administration

DTH testing will be performed at the last visit (Week 8). An injection of 0.1mL of a 4.0mg/mL Vacc‑4x should be administered intradermally at the front of left arm. The DTH test should be performed by the investigator, study nurse, or other clinician experienced in the techniques of intradermal injection. The DTH test results will be evaluated 48 hours after the tests are performed. For each DTH test, evaluation of the injection site at 48 hours will include palpable skin induration and skin erythema. A positive DTH test is defined as an area 10mm2 (either induration or erythema). Study personnel will record DTH results in the subject’s source documents and transcribe them into the CRF. For subjects whose DTH reactions are measured by someone other than study personnel, the investigator is responsible for collecting and recording the result; use of a prepared form completed by the alternative evaluator at the time of the reading is strongly recommended and should be filed with the subject’s source documents.

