### T-cell response

Blood samples (approximately 30 mL) will be drawn and the peripheral blood mononuclear cells (PBMC) separated. The PBMC will be frozen at -150°C, optionally will a fraction of fresh PBMC be tested. T-cell response to the Vacc-4x peptides will be measured in vitro by T cell activation assays (proliferation, cytokines) using flow cytometry (see assay [(Kvale, 2005)](#Kvale2005) and/or ELISPOT. Optionally, proinflammatory and inhibitory cytokines as well as tests for cytotoxicity (degranulation, secretion of Granzyme B or equivalents). T-cell proliferative responses will be compared with data reported in the preceding study CTN B-HIV-2/2002.

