## Statistical methods

Analyses will be based upon an intent-to-treat approach. In general continuous variables will be described using number of observations (N), mean, median, standard deviation (SD), minimum (min), maximum (max), Categorical data will be presented using counts (N) and percentages (%). Subjects without a baseline or a post-baseline assessment for a particular endpoint will not be included in the analysis of change from baseline for that endpoint. All statistical analyses will be performed using SAS Software Version 9.2 or higher. P-values will be reported as 2-sided p-values. All confidence intervals will be reported using traditional 95% two-sided intervals. No adjustment for multiple comparisons will be made.

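### Section 11.6.3 assigns baseline-adjusted models to DTH area, which is measured only once at Week 8, and the protocol does not settle which comparator DTH is read against

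*Protocol*

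**What the plan says.** **Method.** Section 11.6.3 describes the analysis for CD4 counts. Baseline is the "mean of screening and week 1 [Baseline] values". Week 8 values and changes from baseline are both to be "compared among the treatment arms using analysis of covariance (ANCOVA) including the baseline value in the model". Linear models for repeated measures then explore the course over time. For the secondary endpoints the section adds: "Continuous endpoints will analyze using the same approach as described above". It makes no exception. Binary endpoints get a Cochran-Mantel-Haenszel test and a normal-approximation binomial analysis. Section 11.6 adds: "Subjects without a baseline or a post-baseline assessment for a particular endpoint will not be included in the analysis of change from baseline".

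**DTH.** Section 3.2.2 lists DTH as an efficacy endpoint in two forms: the areas of induration and erythema in mm2, and a positive test at 10 mm2 or more. On timing, section 8.2.1 says: "DTH testing will be performed at the last visit (Week 8". The flow chart in section 4.1 and the Visit 6 list in section 7.3.3 agree, and no earlier DTH test is scheduled.

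**Comparator.** Section 3.1.2 sets the DTH objective "in comparison to DTH from unvaccinated patients on effective ART (data from preceding study", without identifying that study. The synopsis states the same objective with no comparator. Section 8.2.3 says: "T-cell proliferative responses will be compared with data reported in the preceding study". Section 11.6.3 describes the Vacc-4x doses relative to Endocine alone.

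**Viral load.** Section 5.2 requires: "Documented viral load (HIV-1 RNA) less than 50 copies/mL for the last six months". ART continues throughout (section 2.7). Viral load is a safety endpoint in section 3.2.1 and is absent from the efficacy endpoints in section 3.2.2. Yet it is a secondary objective in section 3.1.2 and is named at the start of section 11.6.3.

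**The concern.** The protocol fixes a method for DTH area that the visit schedule makes impossible. Any between-arm analysis of DTH area would therefore depart from the written plan and might be chosen after the Week 8 data are in.

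The choice of comparator matters for the same endpoint. All subjects are HIV-infected, and section 2.1 describes natural immune responses to p24. Without a pre-vaccination DTH reading, a contrast with earlier patients cannot separate a vaccine effect from existing reactivity, or from differences in reader or population. The Endocine-only arm is randomised and has the same test at the same visit.

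For viral load, eligibility removes most of the room in which a fall could be seen. A mean change from baseline would then say little, whatever model is used.

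**Working it through.** **Design figure.** Sections 4.1 and 11.1 give 4 arms of 6 subjects: 4 x 6 = 24, as stated. The protocol gives no power figure to reproduce.

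**DTH area against the assigned models.** The ANCOVA design has 5 columns: an intercept, three arm indicators and the baseline value.

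| Assigned model | Needs | DTH area has |
| --- | --- | --- |
| ANCOVA of Week 8 value | a baseline covariate | none |
| ANCOVA of change | baseline and Week 8 | Week 8 only |
| Repeated-measures model | several readings per subject | one reading |

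None can be fitted. Without the baseline column the design has rank 4 and leaves 24 - 4 = 20 residual degrees of freedom with complete data. The Week 8 comparison of arms is then estimable, with Endocine-only as reference.

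**DTH positivity at six per arm.** The normal-approximation interval is p ± 1.96 x sqrt(p(1 - p)/6).

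- At 0/6 or 6/6, p(1 - p) = 0, so the interval has zero width.
- At 1/6, the half-width is 1.96 x sqrt(0.1667 x 0.8333/6) = 0.298. The interval runs from -0.13 to 0.46, so its lower limit is below zero.
- The exact two-sided 95% upper limit for 0/6 is 1 - 0.025^(1/6) = 0.459, so the exact interval is 0 to 46%.

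**Resolution of an exact rank test.** Two arms of 6 can be ranked in C(12,6) = 924 ways. Without ties, the smallest two-sided p-value is 2/924 = 0.002, so the test is usable at this size.

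**Viral load.** The documents give no assay limit and no rule for values below it, so two cases have to be assumed.

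- *Every baseline is reported at one limit.* The baseline column is a multiple of the intercept, so the 5-column design has rank 4. The baseline slope is not estimable and the model reduces to a plain four-arm comparison.
- *The laboratory reports numbers below 50* (20 to 49 assumed). The rank is 5 and the model runs. A subject whose baseline is below 50 can then fall by less than 50 copies/mL.

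If a share q of subjects has a baseline that is not at the limit, the chance that all 24 baselines are identical is (1 - q)^24:

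| q (assumed) | 0% | 5% | 10% | 20% |
| --- | --- | --- | --- | --- |
| Chance | 1.00 | 0.29 | 0.08 | 0.005 |

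The model will therefore often run. The trouble is censoring more than estimability.

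**The case against.** The primary objective is safety. The sample size is descriptive by declaration, and section 11.6.3 says that the focus is description. No dosing or safety decision in the protocol rests on the DTH or viral-load ANCOVA. All of this stands, and it limits the severity.

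Several stronger readings are tempting, and the documents do not support them.

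- *DTH and viral load have no valid analysis.* Section 11.6.3 opens with descriptive summaries of the efficacy endpoints, and DTH positivity has a binary route that needs no baseline.
- *None of the 24 subjects enters any DTH analysis.* The exclusion in section 11.6 is confined to change from baseline. It does not touch the Week 8 comparison, where only the covariate is missing.
- *The viral-load ANCOVA cannot be run.* That holds in full only if every baseline is reported at one limit, which the documents do not say. Nor does eligibility guarantee a Week 1 value below 50, and Week 1 is half of the baseline mean. It is also unclear whether the sentence on continuous endpoints covers viral load, given its listing under safety.
- *The earlier study replaces the randomised control.* No section says so. Sections 3.1.2 and 8.2.3 name earlier data, and section 11.6.3 uses Endocine-only.
- *Analysing both the Week 8 CD4 value and the change is an error.* With baseline as covariate, the two give identical arm effects. The pair is redundant but harmless.

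**Conclusion.** The point holds in a limited form, at moderate severity. The assigned ANCOVA, change analysis and repeated-measures models cannot be fitted to DTH area. That follows from the schedule alone and needs no assumption. What remains is descriptive summary and a binary analysis whose normal approximation breaks down at six per arm.

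The DTH comparator is unreconciled between section 3.1.2, the synopsis and section 11.6.3. This is an inconsistency, since a randomised comparison is already provided for. Enrolment runs in dose steps (section 4.1), so concurrency with the Endocine-only arm means the same study, test and visit, with calendar time only roughly matched.

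For viral load, the supported statement is that mean change is likely to be heavily left-censored and uninformative. This rests on eligibility below 50 copies/mL and continued ART. How far the ANCOVA fails depends on a reporting convention that is not given.

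**What to change.** - **Section 11.6.3, DTH area.** Exempt it from the baseline term, the change analysis and the repeated-measures models. Compare Week 8 areas of each Vacc-4x arm with the Endocine-only arm, for example by an exact Wilcoxon test with a Hodges-Lehmann shift estimate. Other rank-based or exact methods would serve as well.
- **Section 11.6.3, DTH positivity.** Report it by arm with exact binomial intervals in place of the normal approximation.
- **Sections 3.1.2 and 8.2.3, and the synopsis.** State that the Endocine-only arm is the comparator and that earlier-study data are descriptive context. Identify the preceding study meant in section 3.1.2.
- **Viral load.** Summarise the number and percentage of subjects at or above 50 copies/mL after dosing, with an exact interval, in place of mean change. State how values below the assay limit are handled. Reconcile the listing as a safety endpoint in section 3.2.1 with its place in sections 3.1.2 and 11.6.3.

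The cost is wording in these places. No new data, visits or subjects are needed.

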### Efficacy endpoints

- Immune response – T cell immunogenicity:

T-cell responses to Vacc-4x at screening and week 1 compared to week 8.

- CD4 counts at screening, week 1, week 4 and week 8 (Termination).
- DTH (both induration and erythema) at week 8 in terms of observed areas (mm2) and also in terms of a positive test, defined as an area ≥10 mm2.

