## Determination of sample size

It is decided that 6 subjects should be included in each of the four study arms. As this is a pilot study, the sample size has primarily been determined to provide descriptive statistics for the safety and efficacy parameters.

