## Handling of missing data

Missing data will not be imputed and all summary statistics will be reported based upon observed data.

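### With six subjects per arm, the normal approximation prescribed for binary endpoints gives zero-width intervals at 0/6 and 6/6 and per-arm coverage below 95% at every true rate

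*Protocol*

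**What the plan says.** Section 11.1 fixes the arm size: "It is decided that 6 subjects should be included in each of the four study arms". It adds: "As this is a pilot study, the sample size has primarily been determined to provide descriptive statistics for the safety and efficacy parameters". No power or precision calculation and no expected response rate is given.

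Section 11.6 sets the confidence level for the whole plan: "All confidence intervals will be reported using traditional 95% two-sided intervals". Section 11.4 states: "Missing data will not be imputed and all summary statistics will be reported based upon observed data". The denominator for a binary endpoint is therefore at most six per arm.

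Section 11.6.3 names the method: "Binary endpoints will be summarized using the Cochran-Mantel-Haenszel test and the normal approximation to the binomial distribution". It notes the small sample only when it describes the models for continuous outcomes: "Given the small sample size, the focus of these will be primarily to describe the changes associated with the different Vacc-4x doses". No exact or small-sample method for binary data appears anywhere in the protocol.

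The one binary efficacy endpoint explicitly defined is in section 3.2.2. DTH at week 8 is reported as an area and "also in terms of a positive test, defined as an area ≥10 mm2".

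**The concern.** The normal approximation estimates the standard error of a proportion from the observed proportion itself. With six observations that estimate is unstable, and it is exactly zero when all subjects or none respond.

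The plan's declared purpose is description, so an interval shown beside a proportion is a main part of what the reader takes away. An Endocine-only arm with no positive DTH tests would carry an interval from 0% to 0%, although six negatives are compatible with a true rate of up to 46%. An arm with six positives would carry an interval from 100% to 100%, although the data are compatible with a rate as low as 54%.

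This is a method that the protocol names, so it is not a detail left open for a later analysis plan.

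**Working it through.** **Inputs.** n = 6 per arm (section 11.1); two-sided 95%, so z = 1.96 (section 11.6); normal approximation to the binomial (section 11.6.3). The true response rate p is not in the protocol, so a range is shown as an assumption. There is no sample-size calculation to reproduce: 4 × 6 = 24 agrees with section 4.1.

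**Step 1: intervals for each possible result.** Wald: p̂ ± 1.96·√(p̂(1 − p̂)/6). At 1/6, √(0.1667 × 0.8333/6) = 0.152 and 1.96 × 0.152 = 0.298, so the interval is 16.7% ± 29.8%. At 0/6 and 6/6 the square root is zero. Clopper-Pearson at 0/6 has upper limit 1 − 0.025^(1/6) = 45.9%.

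| Positive | Wald 95% | Clopper-Pearson 95% |
|---|---|---|
| 0/6 | 0 to 0% | 0 to 45.9% |
| 1/6 | −13.2 to 46.5% | 0.4 to 64.1% |
| 2/6 | −4.4 to 71.1% | 4.3 to 77.7% |
| 3/6 | 10.0 to 90.0% | 11.8 to 88.2% |
| 4/6 | 28.9 to 104.4% | 22.3 to 95.7% |
| 5/6 | 53.5 to 113.2% | 35.9 to 99.6% |
| 6/6 | 100 to 100% | 54.1 to 100% |

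Only 3/6 gives a Wald interval that has width and stays inside 0–100%.

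**Step 2: actual per-arm coverage.** Coverage at p is the sum of C(6,x)·p^x·(1 − p)^(6−x) over those x whose interval contains p.

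- At p = 10%, the Wald intervals for x = 1, 2 and 3 contain p: 0.354 + 0.098 + 0.015 = 0.467. The missing part is almost all from 0/6, which has probability 0.9^6 = 0.531.
- At p = 50%, x = 2, 3 and 4 contain p: (15 + 20 + 15)/64 = 0.781.

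The chance of a zero-width interval is p^6 + (1 − p)^6.

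| Assumed true rate | Wald coverage | Clopper-Pearson coverage | Chance of zero width |
|---|---|---|---|
| 5% | 26.3% | 99.8% | 73.5% |
| 10% | 46.7% | 98.4% | 53.1% |
| 20% | 72.1% | 98.3% | 26.2% |
| 30% | 87.1% | 98.9% | 11.8% |
| 40% | 91.2% | 99.6% | 5.1% |
| 50% | 78.1% | 96.9% | 3.1% |

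The values are symmetric about 50%. Over a grid of rates from 0.1% to 99.9%, Wald coverage is at most 91.2% and Clopper-Pearson coverage is at least 96.6%.

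**Step 3: differences between two arms, 6 v 6.** The Wald interval is d ± 1.96·√(p̂₁(1 − p̂₁)/6 + p̂₂(1 − p̂₂)/6), enumerated over all 49 outcomes.

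| Assumed true rates | Wald coverage |
|---|---|
| 90% v 5% | 60.3% |
| 90% v 10% | 71.2% |
| 70% v 20% | 82.2% |
| 30% v 10% | 84% |
| 50% v 50% | 85.4% |
| 20% v 20% | 93.4% |
| 10% v 10% | 98.2% |
| 5% v 5% | 99.7% |

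Newcombe's interval covers 95% at 90% v 5%, 98% at 30% v 10% and 90.5% at 90% v 10%. The high Wald coverage at equal low rates is partly an artefact. At 10% v 10%, both arms show 0/6 with probability 0.9^12 = 28%; the interval is then [0, 0], which counts as covering only because the true difference is exactly zero.

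**The case against.** **The stakes are limited.** The primary objective is safety. The affected endpoint is secondary, DTH is also reported as an area in mm², and no decision rule is tied to the binary interval. Section 11.6 also calls for counts and percentages, so a reader will see that the arm has six subjects and may well recognise a [0%, 0%] interval as absurd. This stands, and it limits how serious the point is.

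**The protocol does not say Wald.** A score interval also rests on a normal approximation and would not collapse at 0/6. That is true, but Wald is the ordinary reading of the wording, and no score interval is named.

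**The shortfall varies.** It is about 4 points near a true rate of 40% or 60%, and differences between two low, equal rates are not under-covered. This stands, and the claim is limited accordingly.

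A reader might also infer four stronger things that the protocol does not support:

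- *That 0/6 or 6/6 is the likely result in a particular arm.* No expected DTH rate is given for any arm.
- *That the Cochran-Mantel-Haenszel test inflates false positives, so Fisher's test is required.* With no strata named, the test reduces to a large-sample chi-square, and its p-values can sit well below the exact ones: 4/6 v 0/6 gives 0.019 against 0.061 by Fisher. Its true size at 6 v 6 is nevertheless at most 3.9%, while Fisher's is about 0.6% at a common rate of 50%. The choice is a preference.
- *That adverse event incidence is affected.* Section 11.6.2 prescribes no interval for adverse events.
- *That any alternative interval would do.* Wilson covers 91.2% at a 40% rate and 88.6% at 2%, with a minimum of 83.3%.

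**Conclusion.** The point holds and should be fixed: the rule is wrong as written for proportions in arms of six. The nominal 95% interval never reaches 95% coverage at any true rate, the best value being 91.2%. It has zero width at 0/6 and 6/6, and four of the other five results give a limit outside 0–100%. For differences, coverage is too low when the rates are unlike, but not when both are low and equal.

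Two assumptions carry this: that the normal approximation means the Wald interval, and, for the size of the shortfall, the unknown true rate. The zero-width and out-of-range results need only the first.

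It is not a must-fix. A reader might infer that the trial's main conclusion is at risk. The documents do not support that, because the primary objective is safety and the sentence governs secondary binary endpoints, in practice positive DTH.

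**What to change.** In section 11.6.3, replace the reference to the normal approximation with wording such as: proportions in each arm will be given with Clopper-Pearson 95% confidence intervals; any difference from the Endocine-only arm will be given with a Newcombe or Miettinen-Nurminen 95% interval.

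The cost is one sentence. The intervals are available in the SAS software already specified in section 11.6, and the design, data collection and sample size do not change. The downside is that Clopper-Pearson intervals are conservative and wide at this sample size. Newcombe does not guarantee 95% either (90.5% at 90% v 10%), but at the unlike rates compared it is much closer than Wald. The planned test can stay as it is.

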# study management and ethical and regulatory requirements

## Regulatory approval and Good Clinical Practice

This study will be conducted in accordance with GCP requirements described in the current revision of International Conference on Harmonization of Technical Requirements of Pharmaceuticals for Human Use (ICH) Guidelines and all applicable regulations. Compliance with these regulations and guidelines also constitutes compliance with the ethical principles originating from the Declaration of Helsinki. This study will also be carried out in accordance with local legal requirements.

Before the first subject is enrolled in the study, all ethical and legal requirements must be met.

